### 2.6. Interventions

#### 2.6.1. Routine care

Referring to the 2018 Chinese Guidelines for the Diagnosis and Treatment of CHF (6), the subjects will be given conventional basic treatment to reduce cardiac load and reverse ventricular remodeling, including the use of ACEIs, ARBs, ARNIs, diuretics, β-blockers and other standardized drug therapies. After entering the treatment period, the type and dose of the drugs used for each patient will continue the standard treatment plan before enrollment. If the patient needs to adjust the drug dosage or type due to a change in condition during the treatment period, the drug name, dosage, frequency and time of use, the composite endpoint events and adverse events will be recorded in the CRF table.

#### 2.6.2. Experimental group

Patients in the experimental group will receive routine care plus XLF granules (2 bags at 10 mg each, orally, three times a day, with warm water) for 12 weeks, and the total observation follow-up period will be 24 weeks.

#### 2.6.3. Control group

Patients in the control group will receive routine care plus placebo granules (2 bags at 10 mg each, orally, three times a day, with warm water) for 12 weeks and the total observation follow-up period will be 24 weeks.

#### 2.6.4. Concomitant medication during the trial

During the trial, we do not suggest using other similar TCM with the goal of invigorating qi or promoting blood circulation and diuresis, or any Chinese patent medicines for HF that are stated in the instructions. Concomitant therapy for comorbidities will be allowed during the trial.

#### 2.6.5. Monitoring compliance

The subjects' compliance will be evaluated by recording the distribution and recovery of the medication. Patients with compliance rates equal to or >80% will be considered as having high compliance. Any reasons for not taking the medication will be recorded as well.

### 2.7. Outcome measurements

The time points of the study data collection for outcome measurements are shown in Table 2.

#### 2.7.1. Primary outcomes

The primary outcome is the proportion change in patients with a decrease in serum NT-proBNP of more than 30% after 12 weeks of treatment.

#### 2.7.2. Secondary outcomes

The secondary outcomes will include: (1) Minnesota Living with Heart Failure questionnaire (12); (2) NYHA classification evaluation (13); (3) 6-min walking test (14); (4) TCM symptoms evaluation; (5) the Evaluation Scale of Dampness Syndrome of Traditional Chinese Medicine (15); (6) echocardiography parameters, and (7) clinical events (e.g., hospitalization for worsening heart failure, all-cause death, other major cardiovascular events).

### 2.8. Safety assessments

Information on adverse events (AEs), including the occurrence time, severity, duration, adopted measures, and prognosis, will be recorded truthfully and in detail. Additionally, the investigator will assess every AE recorded to analyze the causality between the AE and the studied drugs. Serious adverse events (SAEs) are defined as events which can cause hospitalization, loss of ability to work, disability, congenital deformity, or death, according to the International Council for Harmonization of Technical Requirements for Pharmaceuticals for Human Use (ICH) guidelines (16). Besides the abovementioned measures, in the incidence of any SAE, the principal investigator will be notified. Additionally, a report will be submitted to the ethics committee and the data and safety monitoring committee (DSMC) within 24 h.

### 2.9. Sample size calculation

Sample size calculation is based on the level of NT-proBNP, the main efficacy indicator. The literature showed that after 12 weeks of conventional basic treatment combined with placebo, NT-proBNP levels decreased by more than 30% in 31.98% of the patients, and after 12 weeks of conventional basic treatment combined with TCM, NT-proBNP levels decreased by more than 30 in 47.95% of the patients (17). Therefore, we estimate that after 12 weeks of conventional basic treatment combined with XLF, the NT-proBNP levels will decrease by more than 30 in 50% of the patients. Thus, assuming α = 0.05 and β = 0.20, the calculated sample size required for each group is 114 cases, after substituting the above values in PASS 11. Considering that 20% will miss visits, the sample size is adjusted to 150 cases in each group.

### 2.10. Statistical analysis

Statistical analysis will be conducted with SAS 9.2 (SAS Institute Inc., USA) in accordance with a pre-established statistical analysis plan. Data analysis for efficacy will be performed following the intention-to-treat (ITT) principle. The full analysis set (FAS) comprises all randomly assigned patients, but rejects those who are wrongly enrolled, or do not receive any assigned treatment or follow-up. The per-protocol set (PPS) includes patients who complete the planned treatment program. The safety set (SS) includes patients who received at least one treatment after randomization and were evaluated for safety. Efficacy analysis will be performed on the FAS and PPS. All baseline demographics will be analyzed on the FAS, and safety evaluation will be performed on the SAS.

The two groups' baseline characteristics will be summarized by descriptive statistics. For the primary and secondary outcomes, a *t*-test or Mann–Whitney *U* test will be employed for continuous variables with normal or unknown distributions; Chi-squared test or Fisher's exact test will be used for categorical variables. Any change across time among the primary or secondary outcomes will be analyzed by the generalized estimated equation model or a mixed-effects model, as appropriate. Sub-group analysis will also be conducted according to the pre-established statistical analysis plan.

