In this study, the proportion of patients whose serum NT-proBNP decreased by more than 30% serves as the primary outcome. NT-proBNP is a cardiovascular neurohormone secreted by ventricular myocytes, which can be used for the diagnosis and differential diagnosis of HF, risk stratification, and prognosis evaluation (26). As the best biomarker in the laboratory, NT-proBNP is easy to measure, accurate and repeatable, and often used to evaluate the clinical efficacy of drugs (27). In addition, NT-proBNP is a sensitive marker for the diagnosis of heart failure, and its level is more than 450 ng/ml; the accuracy of determining patients with CHF can be as high as 96% (11). Guidelines recommend NT-proBNP levels as the most valuable and reliable biomarker for diagnosing heart failure (28). They are used in many diagnoses, risk classifications, and prognostic evaluation of CHF. Studies have shown that CHF-related death risk is positively correlated with NT-proBNP level (29). Additionally, a previous study has suggested that the prognosis of patients with NT-proBNP level decreasing by at least 30% from baseline after treatment is significantly better than that of patients with no significant change or increased NT-proBNP level (30). Therefore, we selected the proportion of patients with NT-proBNP that decreased by more than 30% in serum as the primary outcome for this study.

6MWT can reflect the cardiac function of patients from exercise tolerance. The method is simple, safe, easy to perform, and reproducible, and widely used in systematic reviews of the treatment of CHF with TCM (14, 31). Echocardiography plays a key role in the diagnosis and classification of CHF. Among the various echocardiography indicators, LVEF is the first choice for evaluating left ventricular systolic function (32). Moreover, left ventricular end systolic diameter (LVSDD), left ventricular end diastolic diameter (LVEDD) and inlet ventricular septal thickness (IVST) are the most common indicators for CHF systematic evaluation (32). Additionally, in the systematic evaluation of TCM treatment for CHF, TCM symptoms evaluation, the Minnesota Living with Heart Failure Questionnaire, and improvement of NYHA classification are often used as the evaluation criteria of clinical efficacy (32). Monitoring adverse events and adverse reactions are of great significance for evaluating drug efficacy and guiding clinical medication (33).

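### The between-group test named for categorical outcomes ignores the order of NYHA class; if NYHA is analysed as classes I to IV, a rank or proportional-odds method should be named instead

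*Protocol article*

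**What the plan says.** Section 2.10 of the protocol article gives one rule for both outcome levels, opening with "For the primary and secondary outcomes, a". A t-test or Mann-Whitney "test will be employed for continuous variables with normal or unknown distributions". For the rest, "Chi-squared test or Fisher's exact test will be used for categorical variables". No method is named for ordered categories.

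The next sentence adds a longitudinal provision: "Any change across time among the primary or secondary outcomes will be analyzed by the generalized estimated equation model or a mixed-effects model, as appropriate". It states no link function or distribution. The section also refers to a pre-established statistical analysis plan, which is not at hand.

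Section 2.7.2 lists NYHA among the secondary outcomes only as "2) NYHA classification evaluation (13", with no scoring rule. Table 2 schedules NYHA class at baseline and at weeks 4, 8, 12 and 24. Section 2.2.3 limits entry to classes II to IV, so class I can be reached only after entry. The Discussion says that "improvement of NYHA classification are often used as the evaluation criteria of clinical efficacy".

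**The concern.** NYHA class is an ordered category and not a continuous variable. Read as written, section 2.10 therefore sends it to a chi-squared or Fisher test, and the only rank test in the section is kept for other variables.

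On a two-arm by four-class table, the chi-squared test has 3 degrees of freedom. Its p-value does not change if the class labels are shuffled. A small p-value says that the two distributions differ, but not that patients on XLF moved to better classes. The clinical question, as the Discussion frames it, is about improvement.

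At stake is some power to detect a general shift toward better classes, and a test result that does not itself answer the question of benefit. The primary outcome is binary, so the chi-squared rule suits it, and neither that outcome nor its sample size is affected.

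**Working it through.** **1. Inputs from the article.** Section 2.9 calculates the sample size "assuming α = 0.05 and β = 0.20". It takes a control response of 31.98% ("NT-proBNP levels decreased by more than 30% in 31.98% of the patients") and an XLF response of 50%, and arrives at 114 per group, raised to 150 for 20% missed visits. It gives no NYHA distribution, effect size or power.

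**2. The plan's own figure.** For two proportions with unpooled variance, two-sided 0.05 and 80% power:

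n = (1.960 + 0.8416)² × [0.3198 × 0.6802 + 0.50 × 0.50] / (0.50 − 0.3198)² = 113.007, rounded up to **114**.

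This matches. After 20% loss, 150 × 0.8 = 120 per arm are evaluable, so 120 and 150 per arm are used below.

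**3. Degrees of freedom alone.** Take an effect that a 1-df test detects with 80% power (noncentrality 2.8016² = 7.85, two-sided 0.05). With the same noncentrality, power from the noncentral chi-squared distribution is:

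- 1 df (ordinal test): 80.0%
- 2 df (three classes): 70.9%
- 3 df (four classes): 64.5%

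Over all noncentralities, the gap from 1 df peaks at 17.0 points for 3 df and 10.5 points for 2 df.

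**4. Simulation with assumed NYHA data.** The assumed week-12 control distribution over I/II/III/IV is 10/50/33/7%. The XLF distribution follows from a common odds ratio (OR) for a better class: each cumulative odds is multiplied by OR. For OR 1.8:

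- the control cumulative proportions 0.10, 0.60 and 0.93 have odds 0.111, 1.5 and 13.29
- multiplied by 1.8, these become 0.20, 2.70 and 23.9
- the XLF distribution is then 16.7/56.3/23.0/4.0%

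Pearson chi-squared on four classes was compared with the tie-corrected Mann-Whitney test, with 20,000 trials per scenario and 120 per arm:

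| OR | Chi-squared | Rank test | Points lost |
|---|---|---|---|
| 1.3 | 12% | 19% | 7 |
| 1.5 | 25% | 37% | 12 |
| 1.8 | 48% | 66% | 18 |
| 2.0 | 63% | 79% | 16 |
| 2.5 | 88% | 95% | 7 to 8 |
| 3.0 | 97% | 99% | 2 to 3 |

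Five other four-class distributions at 120 per arm, and all six at 150 per arm, lose 11.5 to 18 points for OR 1.5 to 2.0. Outside that range they lose less: 6 to 8.5 points at OR 1.3, 2 to 12 at OR 2.5 and 0.3 to 6 at OR 3.0. A Monte Carlo Fisher test gives a similar loss (48% against 66% at OR 1.8). With no effect (OR 1), both tests reject in about 5% of trials.

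**5. Where the loss shrinks or reverses (120 per arm).**

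- Three occupied classes, for example 55/38/7%: OR 1.5 gives 27% against 35%, OR 1.8 gives 50% against 61%, and OR 2.0 gives 64% against 74%. The loss is about 8 to 11 points.
- Two categories (improved yes/no): 61% against 61% at OR 1.8. There is no loss.
- Non-uniform shift in which only class III moves to II (33% falls to 18%): chi-squared 64%, rank test 46%. The rank test does worse.

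**The case against.** The strongest case on the other side has four parts.

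- **The four-class table is an inference.** Section 2.10 does not mention NYHA and section 2.7.2 does not give its scoring. The Discussion's reference to improvement could equally describe a binary endpoint, for which chi-squared or Fisher is suitable and nothing is lost. This stands, and the point is conditional on NYHA being kept as classes.
- **Detail of this kind may be in the analysis plan.** That is possible for the scoring. But the article is not silent on the tests: it names them and gives their scope, and the rank test is confined to continuous variables. If the analysis plan says otherwise, the two texts should be made to agree.
- **The GEE or mixed-model sentence could carry an ordinal model.** It could. But it concerns change over time, leaves the link open, and does not withdraw the between-group test in the sentence before it.
- **The simulated scenarios favour the rank test.** Proportional odds, four occupied classes and odds ratios near the peak of the gap all do so. The comparison is also unadjusted, so it does not measure a model adjusted for baseline class. This stands as a limit on the size claimed.

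A reader might infer that the trial will lose a fixed amount of power on NYHA, or that its NYHA result would be invalid. The article supports neither. It contains no NYHA assumptions from which a definite loss could follow, and the named test holds its type I error. Direction can also be read from the class proportions by arm, although the test itself does not assess it. Nor does the article rank NYHA above the other secondary outcomes.

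**Conclusion.** The point holds in conditional form. As written, section 2.10 gives an ordered outcome an unordered test, if NYHA is analysed as classes I to IV. With four occupied classes, a uniform proportional-odds shift with an odds ratio of about 1.5 to 2.0, and 120 to 150 per arm, the cost is about 12 to 18 points of power. None of the NYHA distributions or effect sizes comes from the article, and section 5 of the working shows how far the figure moves when they change. It is a minor improvement to one secondary outcome and has no bearing on validity.

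**What to change.** In section 2.10, limit the chi-squared and Fisher rule to binary and unordered categorical variables, and state how NYHA is scored. If it is kept as classes, compare the arms at week 12 (and week 24) by one of:

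- a Wilcoxon / Cochran-Mantel-Haenszel row-mean-score test stratified by baseline class
- a proportional-odds model adjusted for baseline class, reporting the common odds ratio with its 95% confidence interval

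If the repeated visits are modelled, specify a cumulative-logit link in the planned GEE. Settle the choice before unblinding.

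The cost is a sentence or two of analysis text, with no new data, visits or patients. There are two downsides: the summary odds ratio relies on proportional odds, and a rank test can lose power when the effect is not a general shift across classes. Tabulating the class proportions by arm alongside the test would show such a pattern.

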### 2.4. Randomization and allocation concealment

Through the central randomization system, the patients will be randomly divided into a Xin-Li-Fang group and a placebo group at a 1:1 ratio. Stratified by the central stratification method, we will use SAS 9.2 statistical software to generate random numbers and the random assignment results. The investigators will obtain the randomized number and drug number by a sequential number in the central randomization system. All center numbers, sequence numbers, randomization numbers, and drug numbers will be managed by the statistical unit.

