Heart failure is the end-stage manifestation of many heart (and non-heart) diseases. There are various primary diseases that may cause heart failure. In this study, we first established the inclusion and exclusion criteria to screen patients with cardiogenic heart failure. However, patients with cardiogenic heart failure also have many primary diseases which lead to heart failure, such as ischemic heart disease, hypertensive heart disease and arrhythmia. Our previous clinical observation of Xin-Li-Fang showed that Xin-Li-Fang is a compound traditional Chinese medicine preparation with a variety of effective components, and the treatment for heart failure may also be a multi-target and compound mechanism. It has been observed that Xin-Li-Fang may have an effect on heart failure caused by a variety of primary diseases. Therefore, the overall design of our trial did not stratify the primary cause of heart failure, but only focused on cardiogenic heart failure. We did this so that we would not overlook more possibilities of Xin-Li-Fang in the field of heart failure treatment. In subsequent trial analysis, we plan to conduct a subgroup analysis of different causes to further explore whether Xin-Li-Fang has a better effect on heart failure caused by certain primary diseases.

In our study, using a proportion of patients whose serum NT-proBNP had decreased by more than 30% was an innovative design. The serum NT-proBNP concentration in patients with heart failure is high, and this is influenced by renal clearance rate. Additionally, the basal NT-proBNP levels in heart failure patients with different ages and different NYHA classifications varies greatly. Thus, the individual differences in the serum NT-proBNP concentration in included patients are considerable. Based on the above characteristics of NT-proBNP, the baseline NT-proBNP of the patients included in the trial may range from several hundred to tens of thousands. If the decrease in NT-proBNP is directly used as an efficacy indicator for comparison between groups, there may be wide disparities between groups, baseline imbalance, and no comparability. However, patients with a higher NT-proBNP baseline may have a more significant reduction after Xin-Li-Fang intervention, which may lead to a large 95% confidence interval in the outcome indicators, thus preventing the scientific evaluation of Xin-Li-Fang's efficacy and safety.

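### The primary responder comparison uses a test without centre or baseline NT-proBNP; it is valid and meets planned power, but gives up some precision that adjustment would recover at no cost

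*Protocol article*

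**What the plan says.** Section 2.7.1 makes the primary outcome binary: whether NT-proBNP has fallen by more than 30% after 12 weeks. For primary and secondary outcomes, section 2.10 names a t-test or Mann–Whitney test for continuous variables, and says "Chi-squared test or Fisher's exact test will be used for categorical variables". It mentions no stratification and no covariate.

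The same section adds: "Any change across time among the primary or secondary outcomes will be analyzed by the generalized estimated equation model" (or a mixed-effects model, as appropriate). No centre or baseline term is named there either.

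On allocation, section 2.4 says "Stratified by the central stratification method", and then "All center numbers, sequence numbers, randomization numbers, and drug numbers will be managed by the statistical unit". Section 2.1 lists seven centres. Table 2 schedules NT-proBNP and echocardiography at baseline and week 12 only. The quality-of-life score, walk test, TCM scores and NYHA class are measured at several post-baseline visits.

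The Discussion (section 3) says that "the baseline NT-proBNP of the patients included in the trial may range from several hundred to tens of thousands".

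**The concern.** When randomisation is balanced within centres, the arms are forced to be alike on centre. If centres differ in response rate, the true sampling variance of the difference is then smaller than the chi-squared formula assumes. The standard error is too large, and the test rejects less often than its nominal 5%.

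Baseline NT-proBNP is a separate matter. It is not balanced by design, so leaving it out does not distort the type I error. If the baseline level predicts who falls by more than 30%, however, leaving it out forgoes power. Regression to the mean after an entry threshold of 450 pg/ml is one plausible reason that it might, but the documents do not establish it.

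At stake is efficiency in a trial planned at 80% power, using information that will already be in the database.

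**Working it through.** **1. The plan's own sample size.** Inputs from section 2.9: control rate from "NT-proBNP levels decreased by more than 30% in 31.98% of the patients"; XLF rate 50%; and "assuming α = 0.05 and β = 0.20". Sidedness is not stated; two-sided reproduces the figure. With unpooled variance:

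n = (1.960 + 0.842)² × [0.3198 × 0.6802 + 0.50 × 0.50] / (0.50 − 0.3198)² = 113.01, rounded up to **114 per group**, as stated.

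A pooled-variance formula gives 116. So the trial was sized on an unadjusted comparison of two proportions. For 20% loss, 114/0.8 = 142.5, or 143; the plan takes 150, which leaves 150 × 0.8 = 120 evaluable per arm. Power at 120 per arm is 81.4%. Expected control responders are 0.3198 × 120 ≈ 38, so cell counts are ample and chi-squared rather than Fisher would apply.

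**2. What adjustment would change.** This was simulated, because the documents give neither the spread between centres nor the strength of baseline. Set-up: seven near-equal centres, 1:1 within centre, 120 evaluable per arm, marginal rates held at 31.98% and 50% (31.98% in both arms for type I error), two-sided 5%, 2,500 runs per cell. The centre and baseline effects are **assumptions**, given as SDs on the log-odds scale. Each entry is chi-squared / CMH by centre / logistic with centre and baseline.

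| Centre SD | Baseline SD | Type I error (%) | Power (%) |
|---|---|---|---|
| 0 | 0 | 5.0 / 5.0 / 5.5 | 81.6 / 81.4 / 81.6 |
| 0.3 | 0.3 | 4.5 / 4.7 / 5.1 | 81.4 / 82.0 / 82.8 |
| 0.5 | 0.5 | 4.2 / 4.7 / 5.1 | 81.2 / 82.4 / 85.1 |
| 0.8 | 0.5 | 3.8 / 4.7 / 5.1 | 83.6 / 86.4 / 88.0 |
| 0.5 | 1.0 | 3.7 / 4.0 / 4.6 | 82.5 / 83.9 / 89.5 |
| 1.0 | 0 | 3.4 / 5.2 / 5.4 | 83.5 / 87.6 / 87.7 |

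Monte Carlo error is about 0.4 points for type I error and 0.8 points for power.

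**3. Reading the table.**
- Chi-squared type I error is 3.4% to 4.5% in the five rows with a prognostic factor. All five include a centre effect, which is what drives it. In the 0.5/1.0 row CMH also reads low (4.0%), so part of that row's 3.7% is simulation noise.
- CMH gains from 82.0 − 81.4 = 0.6 up to 87.6 − 83.5 = 4.1 points of power: about 1 to 4.
- Logistic regression gains from 82.8 − 81.4 = 1.4 up to 89.5 − 82.5 = 7.0 points: about 1 to 7.
- With no prognostic effect, the three tests agree within simulation error.
- Chi-squared power is never below 81.2%.

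**4. Echocardiography.** This has one post-baseline value, so the repeated-measures model does not help. With equal variances and baseline-to-week-12 correlation r, a change score has variance proportional to 2(1 − r) and ANCOVA to 1 − r². The ratio is (1 + r)/2, which is 0.75, 0.80 and 0.85 for r = 0.5, 0.6 and 0.7. The correlations are assumptions. Against a t-test on the raw week-12 value the ratio would be 1 − r², or 0.75 to 0.51 over the same range. Section 2.10 does not say which form is meant, so the smaller gain is the safer one to quote.

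**The case against.** **The plan delivers what it promised.** The trial was sized on the unadjusted test, and chi-squared keeps 81% to 84% power in every scenario. This stands: the gain is a bonus, not the repair of a shortfall.

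**Stratification by centre is inferred.** The phrase in section 2.4 could describe the central system rather than the stratum. This stands as a caveat. With seven centres, centre numbers among the allocation records and no other factor named, centre is the natural reading, but it needs confirming.

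**A separate analysis plan may add the adjustment.** Section 2.10 refers to one that is not shown. It may do so, but the article names a test for the primary outcome, and the point concerns that named test, not a missing detail.

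**The Discussion already deals with baseline.** A reader might infer that section 3 admits an uncorrected baseline imbalance. It does not: the worry there is about comparing the raw fall in NT-proBNP, and the responder definition is offered as the answer. That removes the problem of scale. It does not remove any dependence of response on baseline level, but the documents do not show that such dependence exists.

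**The repeatedly measured secondary outcomes already have a model.** True. What could be added is baseline and centre as terms.

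**The primary outcome seems to have two rival analyses.** The change-across-time sentence does mention primary outcomes. With a single post-baseline NT-proBNP value, it cannot sensibly supply a second analysis of the responder endpoint. It is loose wording, not a conflict.

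**Conclusion.** The point holds as an efficiency improvement. The named primary test uses neither the apparent randomisation stratum nor a baseline value measured in everyone. Under assumed effects it is mildly conservative (type I error about 3.4% to 4.5%). It gives up about 1 to 4 power points against CMH by centre and about 1 to 7 against logistic regression with centre and baseline. If neither factor is prognostic, the loss is nil.

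Two stronger readings are not supported. The test is not invalid: any error in the standard error is in the conservative direction, so false positives are not inflated. Nor is the trial underpowered by this choice: the stated 114 reproduces, and 120 evaluable per arm give 81.4%.

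The size rests on assumed centre and baseline effects, near-equal centres, a correctly specified model, and centre being the stratification factor.

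**What to change.** - Section 2.4: state that the stratification factor is centre, if it is.
- Section 2.10, primary: logistic regression on treatment, centre and log baseline NT-proBNP, reported as a standardised risk difference with 95% CI; or a centre-stratified CMH test. Keep chi-squared as a sensitivity analysis.
- Limit the GEE or mixed-model sentence to outcomes measured repeatedly after baseline, and include baseline and centre in those models.
- Echocardiography: ANCOVA adjusted for the baseline value.

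Cost: wording only, settled before unblinding. No extra patients, visits or measurements.
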